## Adverse events and data safety and monitoring

19

During the treatment period, clinical care will remain unchanged and will be the responsibility of uninvolved medical staff. The principal investigators will be available by telephone at all times during the trial, and participants will be provided with contact details in case of any adverse events. Participants will also be screened at the time of their clinical visits, including ultrasound and oocyte collection appointments prior ET to ensure that patients are fit to participate in the research. Blood pressure and heart rate would be measured 30 minutes pre- and post-ET. If baseline blood pressure pre-ET is less than 100/60 mm Hg, participation in the study will not be allowed for safety purposes. Adverse events and side effects are recorded 30 minutes post-ET. Serious adverse events will be recorded separately and followed up until resolution. Such events will be reported to the principle investigators, Melbourne IVF research committee, Melbourne IVF Human Research Ethics Committee, Melbourne IVF quality management system, indemnity insurer, and if directed by HREC, to the Australian Therapeutics and Goods Administration.

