**Methods and analyses::**

We will recruit 100 infertile women into one of 2 groups: placebo (n = 50) and nifedipine 20 mg (n = 50). Study participants will be admitted 30 minutes prior to ET and given either tablet after their baseline vital signs have been recorded. They will then undergo ET and be observed for adverse events for another 30 minutes post-ET. The primary outcome will be implantation rate and clinical pregnancy rate. Secondary outcomes include adverse events, miscarriage and pregnancy, and neonatal outcomes. Resulting data will then be analyzed using *t* test, Chi-square test, and multivariate test to compare outcomes between the 2 groups for any statistical significance. This protocol has been designed in accordance with the SPIRIT 2013 Guidelines.

Key PointsSignificant preliminary research has been performed to form the basis for the design of this trial.This is a randomized, placebo-controlled, double-blind trial to assess nifedipine's effect and safety at the time of embryo transfers.This study has the potential to provide a foundation for future large randomized controlled trialsThis trial is a well-designed randomized controlled trial to assess clinically relevant outcomes.Main limitation of this study is that uterine contractions are not measured and existing variability in embryo quality.

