Calcium channel blockers (CCBs) are nonspecific smooth muscle relaxants, predominantly used for the treatment of hypertension in adults. It specifically inhibits the transmembrane calcium influx at the voltage-gated L-type channels.^[24]^ Since these channels are expressed widely throughout body, including the myocardial cells, vasculature smooth muscles, and the myometrium, CCB exhibits multiorgan effects.^[25]^ By inhibiting the slow inward current of the action potential via reducing the intracellular levels of calcium,^[26]^ it decreases the contractility of the smooth muscles and hence causes vasodilation, uterine relaxation, and other effects throughout the body.^[24]^

The most widely used and studied CCB is nifedipine, and there is evidence for safety in pregnancy.^[27–31]^ Nifedipine belongs to a subclass of CCB, namely dihydropyridine, which is selective to vascular over cardiac tissues of about 10:1.^[27]^ Nifedipine, as a CCB, has vasodilatory and potent uterine relaxation properties.^[24]^ It appears that nifedipine is a very safe drug with limited major adverse effects and has demonstrated superiority over other drugs, such as labetolol and β2 adrenoreceptor agonists, in the management of preterm labour or pregnancy induced hypertension consistently.^[24,27–29,32–37]^

As nifedipine is an antihypertensive and has cardiodepressive effect,^[38]^ patients who suffer from hypotensive or compromised cardiovascular conditions are contraindicated to the use of nifedipine.^[34]^ For others, the most common maternal side effects, when nifedipine is used in a therapeutic range, are: transient facial flushing, headache, nausea, tachycardia, and hypotension; less common side effects are: palpitations, dizziness, chest pain, nasal congestion, oedema, and heartburn.^[25,28,37,39–40]^ These side effects are mostly benign and are resolved spontaneously or by withdrawal of administration.^[37,39–40]^ Naturally, adverse events vary according to the total dose of nifedipine^[28]^ and these data arise from studies based on multiple dosing regimen but no data are available for a single dose regimen. Current recommended maximum dosage is 120 mg per day^[31]^ but maximum dose of 160 mg per day has been reported to achieve tocolysis with no increase in maternal side effects in 1 study.^[41]^ Nevertheless, caution should be exercised when prescribing any medication in any clinical scenario.

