## Interventions to be measured

8

This trial will have 2 arms. All capsules will be indistinguishable from each other.(1)Placebo tablet taken once, 30 minutes pre-ET.(2)20 mg immediate release nifedipine tablet taken once, 30 minutes pre-ET

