## Discussion

23

Implantation failure is a major factor limiting the success of IVF/ICSI treatment and excessive UCs is one of the mechanisms contributing to implantation failure. Given nifedipine's tocolytic properties, safety profile, and use in obstetrics practice, it is a promising candidate to improve the outcomes of IVF/ICSI treatment. This trial is essential to confirm the efficacy, side effects, and safety of nifedipine in infertility treatment. If this study confirms that nifedipine favors a positive outcome, we will then proceed to a phase II randomized controlled trial. A phase I trial to investigate the clinical benefits, namely improved implantation and pregnancy rate of nifedipine in IVF/ICSI treatment cycle, has been initiated.

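### Non-serious side effects are actively collected only until 30 minutes after transfer, about one hour after the dose, which is too narrow for the claim to confirm side effects

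*Protocol article*

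**What the plan says.** Four places in the protocol article set the collection of adverse events.

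- **Section 8 (Interventions to be measured)** fixes the active dose: "20 mg immediate release nifedipine tablet taken once, 30 minutes pre-ET". The placebo is taken at the same time.
- **The Abstract** describes the observation period: "They will then undergo ET and be observed for adverse events for another 30 minutes post-ET".
- **Section 19 (Adverse events and data safety and monitoring)** gives the recording point, "Adverse events and side effects are recorded 30 minutes post-ET", and the vital signs, "Blood pressure and heart rate would be measured 30 minutes pre- and post-ET". It adds a route for unsolicited reports, "participants will be provided with contact details in case of any adverse events", and a rule for serious events: "Serious adverse events will be recorded separately and followed up until resolution".
- **Section 10 (Secondary outcome)** lists adverse events first, with dizziness and hypotension as examples. It sets no time window. Miscarriage, pregnancy and neonatal outcomes are listed separately, and section 20 continues follow-up to birth, or until no clinical pregnancy is found.

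Two statements set what the adverse-event data are meant to achieve. Section 1 (Introduction) says that known side-effect data come from repeated dosing and that "no data are available for a single dose regimen". Section 23 (Discussion) says: "This trial is essential to confirm the efficacy, side effects, and safety of nifedipine in infertility treatment".

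**The concern.** The article identifies a gap in knowledge, namely side effects after a single dose, and offers this trial as a means of confirming them. It then schedules one enquiry about non-serious events, about an hour after the tablet. Anything mild that starts later is recorded only if the participant takes the trouble to report it.

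The safeguards in the text serve other purposes. Following serious events to resolution does not pick up flushing, headache, nausea or dizziness, which section 1 lists among the drug's side effects and describes as mostly benign. A contact number yields spontaneous reports, without a known number of women who were asked. Pregnancy and neonatal outcomes are different endpoints, and most arise only in women who conceive. Section 10 has no time window, so scheduled early records and unsolicited later calls could also be merged into one rate that is hard to interpret.

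At stake is what the adverse-event comparison, tested between arms under section 18, can be said to show. A woman who was not asked at the time cannot be asked contemporaneously afterwards.

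**Working it through.** **1. Time from dose to recording.** The article states no figure for this, so there is none to reproduce.

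- Inputs: dose 30 minutes before transfer (section 8); recording 30 minutes after transfer (section 19, consistent with the Abstract); duration of transfer not stated.
- Formula: 30 + duration + 30.
- Result: 60, 70 or 80 minutes for an assumed transfer of 0, 10 or 20 minutes. About one hour is a fair summary.

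**2. Is there a later scheduled enquiry?** None is stated. The clinical visits in section 19 at which women are screened come before transfer. The later contacts implied by section 9 (serum hCG and ultrasound) are described only for efficacy.

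**3. What is followed beyond that point?**

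| Type of event | Collection after 30 minutes post-transfer |
|---|---|
| Serious adverse events | Recorded and followed to resolution (section 19) |
| Miscarriage, pregnancy and neonatal outcomes | Collected (section 10), with follow-up to birth (section 20) |
| Non-serious side effects | Only if the woman reports them |

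**4. Illustration of size.** The article gives no event rates and no onset times, so the event rates and capture shares below are assumptions. Inputs from the document are 50 per arm (section 11) and a two-sided 5% level with chi-square or Fisher exact tests (section 18). Power is the summed probability of all pairs of counts, from two independent binomials with n = 50, for which the test rejects.

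*Scenario A: the same share of events is captured in both arms, with true rates of 30% and 10%. Observed rates are 30% × share and 10% × share.*

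| Share captured | Observed rates | Power, chi-square | Power, Fisher exact |
|---|---|---|---|
| 100% | 30% vs 10% | 73% | 64% |
| 75% | 22.5% vs 7.5% | 59% | 45% |
| 50% | 15% vs 5% | 39% | 24% |
| 33% | 9.9% vs 3.3% | 25% | 11% |

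Expected events in the active arm at half capture: 50 × 0.30 × 0.5 = 7.5, against 50 × 0.30 = 15 with full capture.

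*Scenario B: background events are missed more often than drug-related ones. The true background rate is 10% and the drug excess is 20 percentage points.*

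- 50% of background and 90% of excess captured: 0.10 × 0.5 = 5% on placebo, and 5% + 0.20 × 0.9 = 23% on nifedipine. Chi-square power is 79%, above the 73% with full capture.
- 50% of background and 75% of excess captured: 5% against 5% + 0.20 × 0.75 = 20%. Chi-square power is 66%.

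The effect of the short window therefore depends on which events start late. It can lower the power substantially or raise it slightly, and the document does not say which applies.

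**The case against.** The strongest reply is that safety capture does not stop at 30 minutes. Serious events are followed to resolution, the investigators can be reached by telephone throughout, and pregnancy and neonatal outcomes run to birth. The adverse-event definition has no time limit, so a later telephone report would count. This stands. A reader might infer that the trial cannot deliver any confirmation of safety, or that events are recorded once and never again. The document supports neither reading: it gives one scheduled point and excludes no later reports.

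A second reply is that a journal article condenses a fuller protocol, where a later checklist may sit. That would answer a complaint about silence. Here, however, the Abstract and section 19 both state a specific window, and it is that stated window which is at issue. A later enquiry in an unseen document remains possible.

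A third reply is that the tablet is immediate release, so most effects may begin early, and that nothing in the article shows a material share starting later. This also stands as to size. For the same reason, a reader should not infer that the comparison is biased toward no difference, because scenario B shows otherwise under equally admissible assumptions. Power is in any case a limited yardstick for a convenience sample with no power calculation (section 11).

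Nor does the document show that a null result would be taken as final proof of safety: section 23 makes a favourable result the trigger for a phase II trial.

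**Conclusion.** The point holds for non-serious side effects only. Their one scheduled collection is about 60 to 80 minutes after dosing, for an assumed transfer of 0 to 20 minutes. Later non-serious events depend on self-report. That is too thin a basis for an unqualified statement in section 23 that the trial confirms side effects, particularly as section 1 says single-dose data are lacking. Serious, pregnancy and neonatal safety are not affected.

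The size and direction of the loss cannot be determined from the document. The chi-square power figures (25% to 73% with equal capture in both arms; 66% and 79% with unequal capture) illustrate assumed event rates and capture shares and are not estimates for this trial. The change is worth making because it is cheap and would show how much starts after the first hour.

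**What to change.** - **Section 19:** add a standard adverse-event checklist, asked of every woman while allocation is still blinded, at the serum hCG contact that the primary outcome already requires. A next-day message could be added to shorten recall.
- **Sections 10 and 18:** report events up to 30 minutes post-transfer separately from later events, so that solicited early records and later reports are not pooled.
- **If no later enquiry is added:** restrict the section 23 claim to acute tolerability in about the first hour after dosing, plus serious, pregnancy and neonatal events. Limiting every safety statement to the first hour would go too far, because it would disregard outcomes that the trial does collect.

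The cost is one short form at an existing contact for 100 women, and one message each if that option is taken. The downside is some recall error at the later contact, which should be similar in the two arms while blinding holds.

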## Trial modification and discontinuation

20

In the absence of adverse events, the medication regimen will not be modified once started. If other protocol changes are deemed necessary by the investigating team, ethical approval will be sought from approving Human Research Ethics Committee. Once approved, protocol amendments will be notified to all investigators, administrators, and trial participants.

Patients are permitted to withdraw from study participation at any time. The trial will cease follow-up once patients have given birth or when clinical pregnancy is not detected from the trial treatment cycle.

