## Introduction

1

Assisted reproduction technology (ART), from ovarian stimulation to the choice of catheters in embryo transfer (ET), has benefitted from major advances and improvements in recent years to continue to circumvent human infertility. However, implantation rate (IR) and clinical pregnancy rate (CPR) in women following ET have remained lower than desired. The IR and CPR are dependent on multiple factors such as techniques and materials involved in the ET process, quality of embryo, and also receptivity of the endometrium.^[1]^ Extensive research has been undertaken to understand and to improve the success of ET following in vitro fertilization (IVF)/intracytoplasmic sperm injection (ICSI) cycles.

One of the major limiting factors affecting the success of ET is thought to be the failure of embryo implantation in the uterus. Embryo implantation failure was estimated to be up to 85%^[2]^ and is governed by complex mechanisms depending on the quality of both the embryo and endometrium.^[3,4]^

Although embryonic aneuploidy is thought to be the major embryonic limiting factor for successful implantation,^[3]^ excessive uterine contractions (UCs) has been proposed as the endometrial limiting factor contributing to the reduced IR in IVF/ICSI cycles.^[3–5]^ As contractile or peristaltic activities of the uterus could move the implanted embryo toward the fallopian tube or cervix/vagina^[6]^ or might even expel it completely out of the uterus.^[3,4]^ This peristaltic mechanism toward the fallopian tube has been suggested to be the cause of higher ectopic pregnancy rate seen in ART.^[6,7]^ A recent published study demonstrated that the uterine peristaltic wave frequency before ET was inversely related to CPR in fresh and frozen–thawed cycles.^[7]^

Various pharmacological agents have been investigated to reduce UC since. These include cyclo-oxygenase inhibitors, β2 adrenoreceptor agonists, antiinflammatories, phosphodiesterase inhibitors, progesterone, and antispasmodics^[8–23]^ demonstrating variable results. Atosiban, an oxytocin/vasopressin receptor antagonist, has shown to be the most promising in improving IR and CPR.^[13]^

If excessive UC indeed reduces IR and CPR in women undergoing IVF/ICSI cycles, then it represents a potential target for pharmacological agents to improve the success of IVF/ICSI cycles.

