## Primary outcome

9

(1)IR, defined as the presence of serum human chorionic gonadotropic level >5 IU/L following ET.(2)CPR, defined as the presence of a live pregnancy in the uterine cavity at a transvaginal ultrasound at 6 weeks’ gestation onwards.

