## Secondary outcome

10

(1)Adverse events defined as any unwanted outcomes, such as dizziness or hypotension, reported in this trial.(2)Miscarriage rate defined as loss of a diagnosed clinical pregnancy before 20 weeks gestation.(3)Pregnancy and neonatal outcomes including multiple pregnancy, congenital or chromosomal abnormalities, stillbirth, preeclampsia, delivery before 34 weeks, delivery between 34 and 37 weeks, necrotising enterocolitis, abnormal neurology, placenta praevia, gestational diabetes, low birth weight, admission to neonatal intensive care unit, duration of admission, need and duration of respiratory support, or any other neonatal morbidity reported.

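### Follow-up is set to end at birth, but several listed secondary outcomes arise or are completed only after birth

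*Protocol article*

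**What the plan says.** All references are to the protocol article.

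- **Trial modification and discontinuation (section 20)** sets the end of observation: "The trial will cease follow-up once patients have given birth or when clinical pregnancy is not detected from the trial treatment cycle".
- **Secondary outcome (section 10)** lists pregnancy and neonatal outcomes in one item. Some belong to pregnancy and delivery, such as "stillbirth, preeclampsia, delivery before 34 weeks, delivery between 34 and 37 weeks". The list continues with "necrotising enterocolitis, abnormal neurology, placenta praevia, gestational diabetes" and ends with "low birth weight, admission to neonatal intensive care unit, duration of admission, need and duration of respiratory support, or any other neonatal morbidity reported".
- **Primary outcome (section 9)** counts an implantation when serum hCG exceeds 5 IU/L. The stricter endpoint is "CPR, defined as the presence of a live pregnancy in the uterine cavity at a transvaginal ultrasound" at 6 weeks' gestation or later.
- **Introduction (section 1)** says that peristalsis toward the fallopian tube has been "suggested to be the cause of higher ectopic pregnancy rate seen in ART". Ectopic pregnancy is not a named outcome.
- **Adverse events and data safety and monitoring (section 19)** states that serious adverse events are recorded separately and tracked to resolution.

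**The concern.** The stop rule and the outcome list are both explicit, and they disagree about whether anyone observes the infant after delivery. This is not detail that a condensed article leaves to a fuller document. Nor could an analysis plan repair it, because no analysis recovers data that the protocol says will not be collected.

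Pregnancy and neonatal outcomes are among the specific aims, and the Discussion presents the trial as confirming side effects and safety before a phase II trial. If staff apply the stop rule literally, postnatal morbidity is undercounted. If some obtain infant records and others do not, ascertainment varies from one participant to the next. Either way, a low count of neonatal events could reflect when observation stopped and not how the infants fared.

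The second half of the stop rule raises a smaller question of the same kind. It releases women with a positive hCG and no live intrauterine pregnancy, and that group can include ectopic pregnancies.

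**Working it through.** The protocol gives no sample-size calculation or event rate to reproduce, so the check sets the sections side by side.

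**Step 1. Sort the pregnancy and neonatal list by when each entry can be known.** Counting need for and duration of respiratory support separately, and the closing catch-all as one entry, the list has 16 entries.

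| When known | Entries | Count |
|---|---|---|
| By delivery | multiple pregnancy, stillbirth, preeclampsia, delivery before 34 weeks, delivery at 34 to 37 weeks, placenta praevia, gestational diabetes, low birth weight | 8 |
| Partly at delivery | congenital or chromosomal abnormalities (those visible at delivery or already diagnosed) | 1 |
| Arise or are completed after delivery | necrotising enterocolitis, abnormal neurology, neonatal intensive care admission, duration of admission, need for respiratory support, duration of respiratory support, other neonatal morbidity | 7 |

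Check: 8 + 1 + 7 = 16. The last row holds 6 named entries plus the catch-all.

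**Step 2. Apply the stop rule to the last row.**
- The two durations run from birth or later. With observation ending at birth, neither can be measured.
- Necrotising enterocolitis and abnormal neurology develop or are recognised after birth, so they would generally be missed.
- Intensive care admission and need for respiratory support may be evident at delivery for some infants. Later admissions and later support would not be counted.
- Other neonatal morbidity is by its nature mostly postnatal.

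**Step 3. Look for a section that resolves the conflict.** Methods and analyses (section 4) expects secondary outcome data to be analysed by the planned completion date, but sets no period of collection after birth. Adherence and retention (section 17) asks staff to keep contact until follow-up ends, which is the point that section 20 defines. Neither supplies a postnatal window.

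**Step 4. Trace an ectopic pregnancy with hCG above 5 IU/L and no live intrauterine pregnancy through the definitions.**
- Implantation: yes, because the hCG threshold is met.
- Clinical pregnancy: no, because no live pregnancy lies in the uterine cavity.
- Miscarriage: no, because that outcome requires a diagnosed clinical pregnancy.
- Follow-up: ends, because clinical pregnancy was not detected.

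She is therefore a success on one primary outcome and a failure on the other. Her final outcome is recorded only if the scan shows it or someone reports it as an adverse event.

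**The case against.** The best defence is that the stop sentence is loose drafting. The protocol plainly means to analyse its secondary outcomes, and some of the seven entries can be evident at delivery. The trial is also a convenience sample of 100 women meant to guide larger studies, and neither primary outcome is touched. The intent is credible and the limited reach is correct. But intent does not tell staff when to stop, and no reading of the rule lets a duration of admission be known at birth.

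Three stronger readings are tempting, and the document does not support them.

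- *That every neonatal outcome is lost.* Low birth weight and events evident at delivery remain observable.
- *That ectopic pregnancies would go unrecorded.* Ectopic pregnancy is not a listed outcome, so no stated outcome is lost. The scan that triggers the stop may itself show it. The adverse event definition is broad enough to include it, and serious adverse events are followed to resolution with no cut-off at the scan. A woman with an ectopic alongside a live intrauterine pregnancy would stay in follow-up. The Introduction also reports the link with peristalsis only as a suggestion. What stands is that ascertainment is not assured.
- *That safety is observed only shortly after dosing.* Section 19 does say "Adverse events and side effects are recorded 30 minutes post-ET", but it also provides for serious adverse events and gives participants contact details for reporting. Miscarriages, which the aims count among adverse events, are counted up to 20 weeks. A further scheduled adverse event enquiry would be a preference, not a correction.

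**Conclusion.** The end of follow-up in section 20 contradicts the postnatal outcomes in section 10, and the two must be reconciled. Seven of the 16 pregnancy and neonatal entries are affected. The two durations cannot be obtained at all under the rule as written, and the other five would be undercounted to differing degrees. The sorting in the table assumes the ordinary timing of these events, because the protocol does not define them individually.

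The number of infants concerned cannot be derived, since the protocol gives no expected pregnancy or birth rate. The consequence is limited to secondary outcomes, so this is a correction of moderate weight that leaves the primary comparison intact.

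The early-pregnancy gap is a lesser point. It follows from the definitions in section 9 and the stop rule, and it concerns incomplete assurance of ascertainment, not a demonstrated loss of data.

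**What to change.** 1. Reconcile sections 10 and 20 in one of two ways. Either keep collecting data on each live-born infant until neonatal hospital discharge, or a postnatal age fixed in advance, or remove from section 10 the outcomes that cannot be observed by birth. If the outcomes stay, apply the same end point and source of records to both arms.
2. For every woman with hCG above 5 IU/L, record the final location and outcome of the pregnancy before follow-up closes.

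The cost is an amendment, a few data fields and a modest amount of record follow-up for women who conceive. Consent must cover access to infant records. Because section 21 says participant records hold no directly identifiable information, a secure way to link mother and infant records would also be needed. Removing the postnatal outcomes avoids this work, but the trial would then have little to say about neonatal safety beyond what is known at delivery.
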